## Abstract

**Introduction:**

Stress urinary incontinence (SUI) is a common condition in middle-aged and elderly women, significantly impacting their quality of life. Weakening of pelvic floor muscle function is considered one of the main factors contributing to SUI. Despite the established clinical use of acupuncture therapy in treating stress urinary incontinence (SUI), the exact mechanisms underlying its effectiveness require further exploration. This study aimed to assess changes in pelvic floor muscle function during acupuncture using surface electromyography (sEMG). This trial will focus on investigating whether the mechanism by which acupuncture alleviates symptoms in SUI patients is related to the improvement of pelvic floor muscle function.

**Methods:**

This study will be a randomized, single-blind, and sham-controlled trial. The study will recruit 76 female patients diagnosed with SUI. They will be randomly allocated to two groups: acupuncture and sham acupuncture, in a 1:1 ratio. Each group of subjects will receive 10 min of acupuncture treatment at RN3 (Zhongji). Outcomes will be assessed at three time points: baseline, during intervention, and 10 min post-intervention, using pelvic floor muscle sEMG. The primary outcome will be the difference in mean amplitude (μV) of the sEMG recordings during the 10-second tonic contraction phase between the acupuncture and sham acupuncture groups. Secondary outcomes will include assessments of amplitude, variation coefficient, and relaxation time across the other phases of the sEMG evaluation. The trial will record adverse events related to the intervention.

**Discussion:**

This study aims to observe the real-time impact of acupuncture on pelvic floor muscle function using sEMG and to explore how acupuncture exerts its effects.

**Clinical trial registration:**

https://www.chictr.org.cn/, Identifier ChiCTR2200059686.

## Introduction

Stress urinary incontinence (SUI) is a prevalent pelvic floor dysfunction in women (1). Based on the International Continence Society status report, 25%−45% of women occasionally experience urinary incontinence, with SUI accounting for 50% of all cases (2). A study in 2022 showed that (3), over 8.93 million people in China were diagnosed with SUI. SUI occurs in women of different ages, with the highest occurrence in women who have given birth or reached menopause. Various factors such as obesity, estrogen levels, age, and mode of delivery contribute to its development (4). SUI is caused by a variety of clinical triggers, including coughing, sneezing, and strenuous exercise (5). While SUI is not life-threatening, its symptoms can cause inconvenience in daily life, affect social activities, and even potentially lead to psychological disorders, along with a range of social and economic issues (6).

Acupuncture has been shown to relieve symptoms associated with SUI. Randomized controlled trials and meta-analyses have provided evidence supporting the effectiveness of acupuncture in the treatment of SUI, with acupuncture decreasing the frequency and amount of urine leakage (7, 8). Acupuncture treatment has been included as a complementary and alternative therapy in clinical guidelines (1, 9). Despite the proven effectiveness of acupuncture, the potential mechanism underlying its treatment of SUI remains to be elucidated.

One of the etiological factors leading to SUI is the weakening of pelvic floor muscle (PFM) function. The PFM plays an important role in the supporting structure of the pelvic floor. When the supporting structure of the pelvic floor is unstable, overactivity of the bladder neck and proximal urethra may occur. SUI occurs when the abdominal pressure increases and exceeds the urethral closure pressure (10). A previous case report observed the immediate effect of acupuncture on the supporting structure of the pelvic floor (11). However, there is no direct evidence that acupuncture treats SUI by improving the function of PFM, which requires further study.

Clinical methods for assessing PFM function include vaginal palpation, pelvic floor muscle surface electromyography (sEMG), and pelvic floor ultrasound. Vaginal palpation is subjective, and ultrasound only reflects structural changes. In contrast, sEMG provides an objective measure of muscle unit electrical signals, offering a real-time evaluation of PFM functional changes (12).

In light of the above, we hypothesize that acupuncture may improve the patients' PFM function as a potential mechanism for treating SUI. We will use pelvic floor muscle sEMG to evaluate muscle function and compare the immediate effects of acupuncture and sham acupuncture (SA).

## Methods

### Study design

This trial is designed in accordance with the Standard Protocol Items: recommendations for Interventional Trials (SPIRIT) (13). The trial protocol version is V3.0. It has been approved by the Medical Ethics Committee of Longhua Hospital, Shanghai University of Traditional Chinese Medicine (Approval Number: 2022LCSY008) and registered at the Chinese Clinical Trial Registry (ChiCTR2200059686); any changes in the protocol will be reported. The study flowchart is shown in Figure 1, and the time schedule is shown in Figure 2.

**Figure 1 F1:**
[figure not shown]
Study flowchart. sEMG, surface electromyography, T0, baseline; T1, during intervention; T2, 10 minutes post-intervention.

**Figure 2 F2:**
[figure not shown]
Time schedule T0, baseline; T1, during intervention; T2, 10 minutes post-intervention.

### Patient recruitment

This randomized, sham-controlled, single-blind trial will be conducted at Longhua Hospital, Shanghai University of Traditional Chinese Medicine in Shanghai. Potential patients with SUI will be recruited both online and offline, from outpatient clinics by clinicians, and from recruitment posters on hospital websites. After expressing interest in the study, patients will be screened for eligibility by trained staff using the inclusion and exclusion criteria below. A written informed consent form will be obtained from all participants before they are randomized. They will have the right to withdraw at any time, and their personal data will be used exclusively for this study.

### Participants

#### Criteria for diagnosis

The following criteria will be used for the diagnosis of SUI in female patients (14):

Involuntary external urethral urinary leakage caused by increased abdominal pressure triggered by sneezing, coughing, laughing, exercise, or other events;1-h urine pad test indicating weight gain >1 g;Absence of other urinary symptoms, including frequency or urgency.The severity of SUI is determined by the leakage during the 1-hour urine pad test:

(I) ≤ 1 g (normal);(II) >1 g but <10 g (mild);(III) ≥10 g but <50 g (moderate);(IV) ≥50 g (severe).

#### Criteria for inclusion

Patients with mild to moderate SUI mentioned in the diagnostic criteria above;Married women between the ages of 40 and 70 years;Participants must enroll in the study voluntarily and sign the informed consent form.

#### Criteria for exclusion

History of urinary incontinence surgery;Pelvic organ prolapse ≥ grade II;Residual urine volume > 30 ml;Symptomatic urinary tract infection;Urological deformity;Unable to walk and/or run and/or climb stairs;Acupuncture phobia or metal allergies;Continuing to take medicines (for example, midodrine hydrochloride and duloxetine hydrochloride) that may affect bladder function and/or receiving other urinary incontinence treatment;Serious heart, kidney, liver, brain, or blood system disease, mental disorder, diabetes, medulla spinalis disease, multiple system atrophy, and cauda equina disease;Pregnancy.

### Randomization

This study was designed as a randomized, sham-controlled trial. The randomization sequence was generated by an independent statistician using a computer-generated random number method (SPSS v26.0; IBM Corp., Armonk, NY, USA). Eligible patients were randomly allocated in a 1:1 ratio to either the acupuncture group or the SA group. The allocation sequence was prepared as sequentially numbered cards and sealed in opaque envelopes bearing corresponding identification numbers. After participants were formally enrolled and completed baseline assessments, an independent researcher not involved in the intervention or outcome assessment opened the envelopes sequentially according to the order of enrollment to obtain the allocation information. The group assignment was then promptly communicated to the acupuncturist responsible for delivering the intervention.

Throughout the study, investigators, outcome assessors, and data analysts will be blinded to group allocation. Strict allocation concealment procedures were implemented to minimize potential selection bias. The study design and reporting adhered to the CONSORT guidelines for randomized controlled trials.

### Blinding

Due to the specificity of the intervention, acupuncturists cannot be blinded. The acupuncture needles used in the acupuncture group and the SA group have different lengths, but the length of the needles exposed on the skin is the same to ensure blinding of the sEMG examiners. During the study period, an appointment-based patient consultation system will be implemented, and independent consultation rooms will be provided. Patients participating in the trial will receive the intervention at different time points to avoid mutual communication. Patients will also wear eye masks to ensure blinding. After the intervention, the blinding effect on the patients will be tested using the following method: “Which group do you think you belong to? (A) Acupuncture; (B) SA; (C) Uncertain.” In addition, data entry and statistical analysis personnel will be blinded to the group allocation.

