**Figure 3 F3:**
[figure not shown]
Location of the acupoint. Zhongji (RN3) acupoint placement: fourth of five evenly dispersed intervals from navel to symphysis pubis.

Before the intervention, the acupuncturist will disinfect their hands and RN3 with 75% alcohol. In both groups, a blinding device will be applied to RN3. This device will consist of a sterile, cylindrical polyethylene foam pad (5 mm in thickness, 10 mm in diameter; Suzhou Medical Equipment Factory, China) featuring an adhesive base (Figure 4), designed to maintain the acupuncturist's blindness to the intervention. The feasibility of this blinding device has been previously established (15).

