#### Acupuncture group

For the acupuncture group, the real needle (0.30-mm gauge, 75-mm long, Hwato brand, Suzhou Medical Appliance Factory, China) will be used. The needle will be inserted through an adhesive pad into the skin, with a depth of 25–40 mm at RN3. After the needle is inserted, the acupuncturist will perform rapid alternating clockwise and counterclockwise twisting, as well as slight lifting and thrusting, until the patient experiences De qi (characterized by soreness, numbness, heaviness, and distension). The acupuncture treatment will last for 10 min.

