#### Sham acupuncture group

For the SA group, a placebo needle with a blunt tip (0.30-mm gauge, 25-mm long, Hwato brand, Suzhou Medical Appliance Factory, China) will pierce the adhesive pad without penetration, merely pressing against it, and will be retained in place for 10 min.

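### The stated needle lengths, insertion depth and pad thickness contradict the equal exposed length on which the article rests blinding of the sEMG examiners during the intervention (T1)

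*Protocol article*

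**What the plan says.** The Blinding section accepts that the needles differ in length and relies on what remains visible: "the length of the needles exposed on the skin is the same to ensure blinding of the sEMG examiners". The Randomization section claims more broadly that "investigators, outcome assessors, and data analysts will be blinded to group allocation".

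The dimensions are given under Interventions:

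- **Real needle (Acupuncture group):** "the real needle (0.30-mm gauge, 75-mm long, Hwato brand", and "The needle will be inserted through an adhesive pad into the skin, with a depth of 25–40 mm at RN3".
- **Sham needle (Sham acupuncture group):** "a placebo needle with a blunt tip (0.30-mm gauge, 25-mm long", which "will pierce the adhesive pad without penetration, merely pressing against it".
- **Pad, both arms (text below Figure 3):** "polyethylene foam pad (5 mm in thickness, 10 mm in diameter".

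The Outcomes section sets three sEMG recordings: T0 at baseline, T1 during the intervention and T2 ten minutes after it. The primary variable is the mean amplitude in the 10-second tonic contraction. The article describes eye masks for patients but no drape or screen for the examiner, and its check of blinding asks only patients.

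The text below Figure 3 also says that the pad serves to maintain the acupuncturist's "blindness to the intervention".

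**The concern.** The article names one feature as the examiners' protection, equal visible needle length, and then prints dimensions that do not produce it. This matters at T1, because the needle is then in place while sEMG is recorded. Effects during needling are also what the Abstract and Discussion stress as the aim of the study.

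The primary variable is a contraction that the patient performs, with a professional inserting the probe. An examiner who could tell the arm might, without intending to, handle or encourage patients differently. Since only patients are asked to guess their allocation, loss of examiner blinding would go unnoticed, and it could not be repaired in the analysis.

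**Working it through.** **Figure under test.** The Blinding section implies a difference in exposed length of 0 mm.

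**Inputs.** Real needle 75 mm, depth 25–40 mm (Acupuncture group). Sham needle 25 mm, no skin penetration (Sham acupuncture group). Pad 5 mm in both arms (text below Figure 3). Perpendicular insertion and like handles are assumed, because the text states neither.

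**Formula.** Exposed length above the pad = needle length − pad thickness − depth below the skin.

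**Plain reading** (depth measured from the skin, sham tip resting on the skin):

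- Real, shallowest: 75 − 5 − 25 = 45 mm
- Real, deepest: 75 − 5 − 40 = 30 mm
- Sham: 25 − 5 = 20 mm
- Gap: 30 − 20 = 10 mm to 45 − 20 = 25 mm

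Measured above the skin, the real needle shows 35–50 mm and the sham 25 mm, so the gap is again 10–25 mm.

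**Other readings.** The sham wording leaves open whether the tip reaches the skin or stops in the pad. The depth might also be counted from the top of the pad, which gives 75 − 40 = 35 mm to 75 − 25 = 50 mm for the real needle.

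| Depth measured from | Sham tip | Real above pad | Sham above pad | Gap |
|---|---|---|---|---|
| Skin | On skin | 30–45 mm | 20 mm | 10–25 mm |
| Skin | Just in pad top | 30–45 mm | 25 mm | 5–20 mm |
| Pad top | On skin | 35–50 mm | 20 mm | 15–30 mm |
| Pad top | Just in pad top | 35–50 mm | 25 mm | 10–25 mm |

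Over all four readings the gap is 5–30 mm. The stated 0 mm is not reproduced.

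**What equality would need.** Setting 75 − 5 − d equal to 20 gives d = 50 mm, and setting it equal to 25 gives d = 45 mm. Both lie outside the stated 25–40 mm.

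**Could unequal handles close the gap?** A longer sham handle would add a constant to the sham's visible length. Real exposure spans 40 − 25 = 15 mm, while the sham tip can move at most 5 mm within the pad. One fixed sham can therefore match some insertions but not the whole range.

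**Could oblique insertion close it?** Only if 25–40 mm means vertical depth. With the sham tip on the skin, matching needs 50 mm of needle below the skin, so the angle from vertical would be arccos(40/50) ≈ 37° to arccos(25/50) = 60°. Nothing in the text suggests this.

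**Which recordings are exposed.** T0 is complete before the envelope is opened (Randomization). T2 comes ten minutes after the intervention, and the Discussion has the operator take off the pad when the needle is withdrawn. That leaves T1.

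**The case against.** The subtractions are not in dispute. The strongest case against the point concerns what may be built on them.

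- **Geometry.** Insertion angle and handle lengths are not stated, and Figure 4, which might show them, is not available here. This stands as a caveat. It does not rescue the statement, because the 15-mm depth range defeats a fixed sham whatever the handles, and no oblique insertion is described.
- **Visibility.** A reader might infer that examiners will see the needle and know the arm. The article does not say so. It does not say where the examiner stands or whether RN3 is in view, and a condensed article may leave room procedure to the full protocol. What stands is narrower: the one safeguard stated for T1 fails on the article's own figures.
- **Bias.** A reader might infer that every T1 reading in all 76 participants is biased. This is not shown. Under Outcomes, patients follow the device's instructions and the instrument records the signal, which limits an examiner's influence. Some influence remains possible, but its size cannot be derived from the document.
- **Time point.** A reader might take T1 to be the designated primary time point. The article designates none. T1 matters because effects during needling are the stated interest.
- **Acupuncturist blinding.** The phrase below Figure 3 conflicts with the Blinding section, with the limitations paragraph of the Discussion, and with the Randomization section, where the acupuncturist is told the assignment. It reads as a drafting slip and has no bearing on the examiners. The same holds for the unqualified word investigators under Randomization.

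**Conclusion.** The contradiction holds. On the stated dimensions the real needle shows 10–25 mm more than the sham on the plain reading, and 5–30 mm more over all readings, against a claimed difference of 0 mm. This rests on perpendicular insertion and like handles. Dropping the assumption about handles still leaves a 15-mm range of real exposure that a nearly fixed sham cannot follow.

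The article's only stated protection of the sEMG examiners at T1 therefore does not work as written, and an examiner with RN3 in view could infer the arm. The documents do not establish that examiners are in fact unblinded or that the primary outcome is biased.

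**What to change.** 1. Reconcile the Blinding section with the needle and pad descriptions under Interventions, so that the claim about exposed length agrees with the stated lengths, depth and pad. This review proposes no needle length or depth.
2. Do not rely on exposed length for blinding, however the passages are reconciled. Keep the examiner away during needling. Before the T1 recording, have RN3 hidden in both arms behind the same opaque screen or drape, kept clear of the needle. State this in the Blinding section.
3. As a minor correction, delete the statement below Figure 3 that the pad keeps the acupuncturist blind.
4. Optionally, record the examiner's guess of allocation alongside the patient's.

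The cost is a screen or drape, a line in the examiner's procedure and a short delay at T1, plus one case report form item if the examiner's guess is recorded. The screening has to be in place before T1 data are collected.

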### Interventions

In order to ensure the consistency of interventions, all acupuncture treatments will be carried out exclusively by a licensed and highly experienced acupuncturist ([name]). Before the intervention, the acupuncturist will be trained in the correct use of the SA tool. All participants will receive a single 10 min acupuncture treatment at RN3, which is situated four-fifths of the way down from the navel to the pubic symphysis (Figure 3).

**Figure 3 F3:**
[figure not shown]
Location of the acupoint. Zhongji (RN3) acupoint placement: fourth of five evenly dispersed intervals from navel to symphysis pubis.

Before the intervention, the acupuncturist will disinfect their hands and RN3 with 75% alcohol. In both groups, a blinding device will be applied to RN3. This device will consist of a sterile, cylindrical polyethylene foam pad (5 mm in thickness, 10 mm in diameter; Suzhou Medical Equipment Factory, China) featuring an adhesive base (Figure 4), designed to maintain the acupuncturist's blindness to the intervention. The feasibility of this blinding device has been previously established (15).

**Figure 4 F4:**
[figure not shown]
Acupuncture and Sham acupuncture manipulation.

#### Acupuncture group

For the acupuncture group, the real needle (0.30-mm gauge, 75-mm long, Hwato brand, Suzhou Medical Appliance Factory, China) will be used. The needle will be inserted through an adhesive pad into the skin, with a depth of 25–40 mm at RN3. After the needle is inserted, the acupuncturist will perform rapid alternating clockwise and counterclockwise twisting, as well as slight lifting and thrusting, until the patient experiences De qi (characterized by soreness, numbness, heaviness, and distension). The acupuncture treatment will last for 10 min.

#### Sham acupuncture group

For the SA group, a placebo needle with a blunt tip (0.30-mm gauge, 25-mm long, Hwato brand, Suzhou Medical Appliance Factory, China) will pierce the adhesive pad without penetration, merely pressing against it, and will be retained in place for 10 min.

### Outcomes

#### The primary outcome

Mean amplitude during the 10-s tonic contraction phase.

#### The secondary outcomes

(1) The mean amplitude in the prerest phase; (2) The variation coefficient in the prerest phase; (3) The maximum amplitude of five rapid contractions; (4) The relaxation time of five rapid contractions; (5) The variation coefficient in the 10-s tonic contraction phase; (6) The mean amplitude in the 60-s endurance contraction phase; (7) The variation coefficient in the 60-s endurance contraction phase; (8) The mean amplitude in the postrest phase; (9) The variation coefficient in the postrest phase.

Pelvic floor muscle sEMG will be measured using the MLD B4Plus (Biological feedback instrument, Mailande Medical Technology Co., Nanjing). Pelvic floor muscle sEMG will collect muscle movement potentials through a vaginal probe, providing insights into the strength, tone, and coordination of PFM (16, 17). The insertion of the vaginal probe will be conducted by a trained professional, with patients following the device's instructions to complete the assessment. The sEMG evaluation consists of five phases, assessing parameters such as amplitude, relaxation time, and the variation coefficient, which are indicative of clinical significance, as shown in Table 1. This assessment aids clinicians in gaining a comprehensive understanding of patients' PFM function.

**Table 1 T1:** Outcomes of pelvic floor muscle sEMG.

Domain	Meaning	Item	Unit
Outcomes			
sEMG in the prerest phase	measure the muscle tension of the PFMs in the resting status	mean amplitude‡	μV
		variation coefficient‡	
sEMG of five rapid contractions	measure the function of the fast-twitch fibers of the PFMs	maximum amplitude‡	μV
		relaxation time‡	s
sEMG in the 10-s tonic contraction phase	measure the function of the slow-twitch fibers of the PFMs	mean amplitude†	μV
		variation coefficient‡	
sEMG in the 60-s endurance contraction phase	measure the endurance of the slow-twitch fibers of the PFMs	mean amplitude‡	μV
		variation coefficient‡	
sEMG in the postrest phase	measure the recovery function of the PFMs	mean amplitude‡	μV
		variation coefficient‡	

†Primary outcome.

‡Secondary Outcomes.

sEMG, surface electromyography.

The sEMG measurements will be recorded at three time points: baseline (T_0_), during intervention (T_1_), and 10 min post-intervention (T_2_).

### Safety evaluation

The occurrence, duration, and severity of adverse events (AEs), such as fainting, broken needles, unbearable itching at needle insertion sites (VAS ≥ 8), severe post-needling pain > 2 h (VAS ≥ 4), abscess, subcutaneous hematoma, infection, other discomforts (i.e., fatigue, dizziness, or palpitations), and how the event is resolved (or not) will be recorded in a Case Report Form (CRF). Serious adverse events are life-threatening events such as hospitalization or severe incapacity. Serious adverse events will be reported to the Data and Safety Monitoring Board within 24 h for a decision on whether or not to continue tracking.

